## Methods

### Study design and setting

This study is a single-blinded, multicenter randomized controlled trial with stratification on frailty levels. The design of the trial follows the recommendations of the Standard Protocol Items: Recommendations for Interventional Trials 2013 Checklist [27]. The study intervention will be executed by trained, certified and registered physical- and exercise therapists in several municipalities in the Netherlands. Vrije Universiteit Amsterdam is the sponsor of this study.

### Participants

The target population consists of community-dwelling older adults (aged ≥65 years) with an increased risk of falls according to the fall risk screening questionnaire [28–30]. All participants should be able to independently execute activities of daily living (e.g., going to the bathroom, dressing and undressing) and walk 100 m. Older adults will be included if they are classified as non-frail or pre-frail based on the phenotype concept introduced by Fried et al. [31]. Table 1 lists the in- and exclusion criteria including the operationalization for each criterion. Potential participants will be excluded if they participated in a fall prevention intervention in the past 6 months, if they are unable to read and understand Dutch, if they have cognitive impairment defined as a score < 19 on the Mini-Mental State Examination [32], or if they have any self-reported uncontrolled comorbid conditions or contraindications for conducting physical exercises during the In Balance intervention (e.g., cardiovascular, neurological and orthopaedic problems).

**Table 1 Tab1:** Inclusion and exclusion criteria

Inclusion criteria	Exclusion criteria
• Adults aged ≥65 years • Classified as non-frail or pre-frail based on the phenotype concept introduced by Fried et al. (weight loss, weak grip strength, exhaustion, slow gait speed and low physical activity) [31] • Living in a community-based setting • Having a potential fall risk, as assed by the fall risk screening questionnaire [28–30] • Able to independently execute activities of daily living and walk 100 m	• Cognition < 19 points on the Mini-Mental State Examination [32] • Not able to read or understand Dutch • Participation in a fall prevention programme in the past 6 months • Self-reported contra-indications for participation in the In Balance intervention

#### Frailty status

Frailty status will be determined at baseline based on the frailty indicators according to Fried and colleagues [31]. The frailty phenotype includes weight loss, weak grip strength, exhaustion, slow gait speed and low physical activity [31]. Weight loss is assessed by self-reported, unintentional weight loss of 5 kg or more in the last year [31]. Grip strength will be assessed using a handheld dynamometer and is calculated as the average of three measurements of the score in kilogram of the dominant hand [33]. Original cut-off points stratified by sex and body mass index will be used to indicate weak grip strength [31]. Exhaustion is considered present if a participant has a score < 75 on the vitality subscale of the 36-Item Short Form Health Survey [34]. Gait speed will be assessed by recording the time in seconds to walk 4 m at usual pace; slow gait is defined using predefined cut-off points, converted to a 4 m distance, stratified by sex and height [31]. Last, low physical activity will be assessed using the International Physical Activity Questionnaire Short Form (IPAQ-SF) and is defined as burning less than 383 or 270 kcal with physical activity per week for men and women, respectively [31, 35]. Participants will be considered as non-frail if they meet none of the criteria and classified as pre-frail when meeting 1 or 2 of the criteria. If participants meet 3 or more of the criteria, they will be classified as frail and will be excluded from this study [31].

### Recruitment, randomization, blinding and treatment allocation

Recruitment will be done via flyers, advertisements in local papers, folders distributed through supermarkets, pharmacists, community centres, general practitioners, at annual flu shots, and via personal invitations by In Balance therapists and general practitioners. Participants will be randomized into the intervention group or the control group using block-randomization to balance the size of the two groups. Randomization will be stratified according to frailty. We aim to include 30–50% of the participants in the pre-frail subgroup and 50–70% in the non-frail subgroup in both the intervention and control group. As soon as one of the subgroups starts to outnumber the other subgroup, we will only target the underrepresented subgroup for recruitment. Two hundred fifty-six sealed envelopes in blocks of 10 (5 envelopes per group) will be prepared by an independent investigator. These sequentially numbered envelopes contain a random computer-generated unique identification number. A second matching envelope contains the group information. All investigators and assessors involved in this study will be blinded to group assignment until completion of statistical analyses. Due to the nature of this study, participants and therapists cannot be blinded to group allocation. Participants will be informed orally about their allocation and therapists will receive the names of those participants who will participate in the In Balance intervention.

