### Trial status

Enrolment into the study will start on September 1, 2021. We plan to complete the recruitment and data collection at baseline by September 2022, with a 12 months follow-up period on falls incidence and incidence of fall-related injuries until September 2023. This study has been registered with the Netherlands Trial Register on 13 February 2021 (NL9248).

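### A single fixed block size of 10, published before enrolment, makes allocation more predictable than it need be, because therapists both invite participants and learn who received the intervention

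*Protocol article*

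**What the plan says.** All of the following is in the protocol article, mostly under Recruitment, randomization, blinding and treatment allocation.

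- **Method.** Allocation is 1:1 in permuted blocks, with one stratification factor: "Randomization will be stratified according to frailty". No stratification by site or therapist is stated.
- **Block size.** "Two hundred fifty-six sealed envelopes in blocks of 10 (5 envelopes per group) will be prepared by an independent investigator". This is one size, with no variation.
- **Envelopes.** "These sequentially numbered envelopes contain a random computer-generated unique identification number", and the group is held in a second, matching envelope.
- **Who knows.** Neither those treated nor those treating are masked: "Due to the nature of this study, participants and therapists cannot be blinded to group allocation". Each person hears their group by word of mouth, and therapists are sent a list of the people assigned to In Balance. Investigators and assessors are stated to stay blinded until the analyses are complete.
- **Who recruits.** Among several routes, people are reached "via personal invitations by In Balance therapists and general practitioners".
- **Timing.** The article is dated 23 June 2021. Under Trial status: "Enrolment into the study will start on September 1, 2021".

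**The concern.** In a 5:5 block of known size, once five allocations to one group have been used, the remaining allocations in that block are fixed. Anyone who knows the block size and can count past allocations can sometimes name the next assignment, and can often guess it better than chance. Here the size is in print, and one role, the In Balance therapist, both invites people and learns who was allocated to the intervention. A therapist who has invited someone personally may also infer that an invitee who enrolled but is not on the intervention list went to control.

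What is at stake is selection at entry. If the timing or choice of invitations came to depend on the expected next allocation, the groups could differ in baseline fall risk. The primary outcome is a count of self-reported falls, which depends on that risk. An intention-to-treat analysis preserves the groups as randomized and so cannot undo a difference created by who was brought forward.

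**Working it through.** The article gives no predictability figure, so there is none to reproduce. The inputs from it are block size 10 with m = 5 per group, stratification by frailty, and 256 participants in total.

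**1. Worst case: every earlier allocation in the block and stratum is known.**
An assignment is certain when one group already has its five. The last t places of a block are all certain with probability 2 × C(10−t, 5)/C(10, 5), where C(10, 5) = 252:

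- t = 1: 1.0000
- t = 2: 0.4444
- t = 3: 0.1667
- t = 4: 0.0476
- t = 5: 0.0079

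The sum is 1.667 per block, which equals 2m/(m+1) = 10/6. That is 16.7%, or 1 in 6. Because 256 = 25 × 10 + 6, the last block is incomplete, and simulation of the whole trial gives 16.3%, about 42 of 256.

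Always guessing the group with fewer allocations so far is right m + (4^m/C(2m, m) − 1)/2 = 5 + (1024/252 − 1)/2 = 6.53 times in 10. That is 65.3%, against 50% with no information.

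**2. The observer's knowledge lags by L allocations in the same stratum** (enumeration of all 252 orderings):

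| L | certain | best guess right |
|---|---|---|
| 0 | 16.7% | 65.3% |
| 1 | 6.7% | 60.3% |
| 2 | 2.2% | 58.1% |
| 3 | 0.6% | 55.9% |

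A plausible lag follows from the stated timeline. 256 participants over about 52 weeks is 4.9 per week. With 30% to 70% in a stratum, that is about 1.5 to 3.4 allocations per stratum per week. The Informed consent section gives each candidate at least one week to decide. An even pace is an assumption; locally batched recruitment would change it.

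**3. The observer sees only some earlier allocations.**
Simulated certain share: 9.6% if 90% are seen, 3.9% at 75%, 0.5% at 50%, and about 0 at 25%. An observer who sees intervention names only, but knows the position in the block, is certain only after the fifth intervention allocation. The expected tail is 5/6 per block, or 8.3% (1 in 12).

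**4. Other fixed sizes, worst case.**
Blocks of 4, 6 and 8 give 33%, 25% and 20%. Ten is less predictable than these.

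**5. Varied sizes.**
Sizes were drawn at random from 8, 10 and 12. The observer knows this set and every past allocation, but not where the blocks end. Simulation of 128 assignments gives about 1.3% certain, against about 16% for fixed 10 in the same simulation. The best guess is right about 65% of the time under both.

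**The case against.** The strongest reply is that no one in the documents is shown to hold the knowledge that the worst case needs. Therapists are sent intervention names only. Recruitment runs across several municipalities and through flyers, local papers, pharmacists, general practitioners and flu-shot sessions, so allocations are made that a given therapist never sees.

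A therapist can act only at invitation. The person then contacts an investigator, is interviewed by telephone, has at least a week to decide, attends in person, consents, and is screened for cognition and frailty. The therapist therefore does not know which stratum's list the invitee will join, and other entrants use up allocations meanwhile. Eligibility is checked by study staff who are stated to be blinded, so softer criteria such as self-reported contraindications do not give therapists a lever. The envelopes are prepared independently, and the group sits in a separate envelope.

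Most of this stands, and it is why 1 in 6 is an upper bound. Two points limit it:

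- The safeguards protect the next envelope from being read. They do not stop its content being deduced from earlier allocations.
- Exposure need not be negligible everywhere. Filling one intervention group of 8 takes about 16 randomizations at 1:1. Where recruitment is local, that is more than a whole block. In addition, when one frailty subgroup outnumbers the other, only the other is recruited, so allocations then come from one list.

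A reader might also infer that recruiting staff carry the envelopes. The article does not say so. Who holds and opens them is a detail that an article may leave to the full protocol, so it is not counted as a fault here.

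**Conclusion.** The fixed, published block size is a real but modest and avoidable weakness. Its size is bounded above by 16.7% certain assignments and a 65% best-guess rate, and both figures require full knowledge of earlier allocations in the block and stratum. For a therapist who sees only local or intervention allocations, or whose invitees are randomized a few allocations later, the certain share is much smaller: 6.7%, 2.2% and 0.6% at lags of 1, 2 and 3. These figures assume properly executed 5:5 permuted blocks in a separate list for each frailty stratum, shared across sites.

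A reader might infer that about 1 in 6 assignments will be known in advance, or that enrolment will be selective. The documents support neither. They show that selective invitation is possible, limited to whom a therapist invites and when. Nor can the guess rates be turned into a bias on the falls comparison, because that needs the size of any shift in entrants' risk, which the documents do not give. The reason to act is that the improvement costs almost nothing.

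**What to change.** Regenerate the allocation list separately for each frailty stratum, with block sizes drawn at random (for example 8, 10 and 12). Do not disclose the sizes to anyone who recruits, screens or assesses. Because the article is already public, withholding the present block size is not an option; only a new list helps.

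The independent investigator who already prepares the envelopes should hold them and release one allocation at a time, after consent, frailty classification and the M0 assessment are recorded.

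The two parts do different work. Varying the sizes lowers worst-case certain assignments from about 16% to about 1.3% but leaves the best-guess rate at about 65%. Lowering that rate depends on limiting who can follow past allocations, so running tallies by group should not reach therapists or recruiting staff.

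The cost is a new list, a few lines of protocol text and a short release step per participant. No extra participants or staff are needed. The largest possible imbalance at the end of a stratum rises from 5 (half a block of 10) to 6 (half a block of 12).

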### Informed consent

When potential participants have shown interest to participate in the study by contacting one of the investigators, they will first be interviewed by telephone on their eligibility according to the in- and exclusion criteria. Eligible participants will receive an extended information letter via mail or email, in which the study procedures, including randomization, will be explained. All potential participants will be given at least one week to consider participation and to approach the investigator for questions. Eligible participants will be contacted by phone and asked whether they want to participate in the study and whether they are willing to be randomized. When eligible participants agree to participate, they are invited to come to a location in the municipality of the participant and give their informed consent for participation in the study. Next, participants will be screened on cognition and frailty according to the criteria of Fried et al. and if they have a score of 19 points or higher on the Mini-Mental State Examination and are classified as non- or pre-frail, the baseline assessment will be conducted [31].

### Intervention

The In Balance intervention is a fourteen-week group programme for older adults at risk of falls and will be provided by registered and certified physical therapists and exercise therapists [36]. The aim of the intervention is to reduce falls by increasing awareness, balance and strength by combining educational and exercise components. The intervention consists of three phases. The first phase (week 1) comprises one information meeting about physical activity, the impact a fall can have on a person’s life and health, and the purpose of the In Balance intervention. In the second phase (week 2–4), there are three weekly educational meetings about increasing awareness of one’s fall risk and balance disturbance, increasing knowledge about how to implement effective fall prevention methods and getting acquainted with the upcoming training weeks. The third phase (week 5–14) consists of a physical exercise programme with two one-hour training sessions per week. Exercises are derived from principles of Tai Chi, with balance and strength elements and with emphasis on standing strong and shifting weight. Education and Tai Chi exercises are known to be effective in reducing the incidence of falls [37–39]. After each session, the participants receive homework, consisting of conducting exercises learned during the training sessions and reading parts of the textbook belonging to the In Balance intervention. Participants are expected to spend about one hour per week on this homework, distributed over several days. The 3 phases of the intervention are summarized in Fig. 1.

**Fig. 1 Fig1:**
[figure not shown]
Overview of the In Balance intervention

### Control group

The control group will receive written general physical activity recommendations in the form of a flyer. This flyer contains advice on physical activity levels, strength and balance for older adults. For example, a minimal amount of 150 min of moderate to vigorous physical activity per week is recommended, distributed over several days. Also muscle and bone strengthening activities such as walking stairs and balance exercises at least twice per week are advised. Moreover, the health benefits associated with physical activity are explained. These recommendations follow the Dutch Guidelines for Physical Activity [40]. To minimize study attrition, participants of both the intervention and control group will receive regular newsletters during the study and a personal advise on (changes in) physical performance after ending of the study.

### Data collection and outcome measures

#### Primary outcome measure

The primary outcome in this study is the number of falls, with or without injuries, assessed with fall diaries and monthly follow-up telephone calls, including questions on the causes, circumstances and consequences of falls. This combination of pro- and retrospective data collection follows guidelines for conducting fall prevention trials [41].

#### Secondary outcome measures

Besides the number of falls and fall-related injuries, positive effects on physical functioning, physical activity, quality of life and other self-reported outcome measures are measured [42]. The secondary outcome measures will be assessed at three time points during the study period; at entry of the study (baseline, M0), after 4 months to determine the short-term effects (M4) and after 12 months to determine the long-term effects (M12). Societal costs will be assessed at M4, after 8 months (M8) and M12. All secondary outcomes are listed in Table 2 and are described in detail below.

**Table 2 Tab2:**
[figure not shown]
Overview of enrolment, intervention, outcome measurements and time of assessments

PS: prior to study, M0: baseline measurement (pre-intervention), W14: 14 weeks after start of the intervention, M4: 4 months after start of the intervention, M8: 8 months after start of the intervention, M12: 12 months after start of the intervention

#### Questionnaires

The participants will receive and fill in questionnaires at their homes. Participants can choose whether they want to receive the questionnaires online (by email) or on paper.

##### Participant characteristics

Demographic characteristics will be determined at M0 and M12, including age, sex, height, weight, marital status, living situation, work, smoking, fall history, use of walking aids, experience with fall prevention interventions, walking, balance, physical activity, use of medication and presence of chronic diseases.

##### Well-being and fall-related concern

At M0, M4 and M12, several questionnaires will be used. General health status will be determined with the 36-Item Short Form Health Survey [34] and the Positive Health Inventory Tool [43]. Empowerment will be determined with the Pearlin Mastery Scale [44] and the General Self-Efficacy Scale [45]. Concern about falling will be determined with the Falls Efficacy Scale International [46]. Fall risk will be measured with the Longitudinal Aging Study Amsterdam Fall Risk Questionnaire [47]. Walking confidence will be determined with the Modified Gait Efficacy Scale [48]. General quality of life will be assessed using the five-level version of the EuroQol questionnaire (EQ-5D-5L) [49]. Last, to measure quality of life from a broader perspective than health alone, the Adult Social Care Outcomes Toolkit will be used [50].

##### Societal costs

For the economic evaluation, societal costs will be assessed using three retrospective 4-month cost questionnaires at M4, M8 and M12. Healthcare, participant and family costs will be measured using the iMTA Medical Cost Questionnaire [51]. Productivity costs related to paid and unpaid work will be assessed using the iMTA Productivity Cost Questionnaire [52].

#### Physical measurements

##### Physical performance

Physical performance will be assessed at a location in the municipality of the participant on the following time points: M0, M4 and M12. To ensure data quality, assessors, who are blinded to group allocation, will be trained to perform the measurements. The following assessments are included:
*Balance* will be measured with the Performance-Oriented Mobility Assessment – Balance, the Four Stage Balance Test and the Timed Up and Go Test. First, the Performance-Oriented Mobility Assessment – Balance evaluates balance during sitting, standing up, standing, eyes closed, rotating and sitting down [53]. Second, the Four Stage Balance Test assesses the ability to stand with the feet together in the side-by-side, semi-tandem, tandem and standing on one foot positions [54]. Third, the Timed Up and Go Test measures the time it takes to stand up from a chair, to walk 3 m, turn around, walk 3 m back, turn around and sit in the chair [55].*Mobility* will be measured with the Performance-Oriented Mobility Assessment – Mobility. This questionnaire evaluates mobility on start of gait, stride length, stride height, stride symmetry, stride continuity, aberrant gait, trunk and foot distance [53].*Muscle Strength* will be measured with the Hand Grip Strength Test and the Timed Chair Stand Test. Hand Grip Strength Grip strength will be assessed using a handheld dynamometer and is calculated as the average of three measurements of the score in kilogram of the dominant hand [33]. Second, the Timed Chair Stand Test measures the time it takes to stand up and sit down from a chair five times as fast as possible without using the arms [56].*Walking Speed* will be measured with the 10 Meter Walk Test [57]. The participants start from rest and walk 10 m at a self-chosen comfortable pace. The score is calculated as the mean time in seconds of 2 attempts.*Aerobic Endurance* will be measured with the 2-min Step Test [58]. The height of the iliac crest and patella is measured and this is marked on the wall. Then tape is placed on the wall half the distance between the two. The participant steps in place, raising each knee to the tape on the wall for as many times as possible in the 2 min period. The number of times the right knee reaches the required height is counted.*Perceived Fatigue* will be scored directly before and after each of the 3 physical performance tests (Timed Chair Stands Test, 10 Meter Walk Test and 2-min Step Test) with the modified Borg’s CR10 scale [59].

